#### *2.10 Will health service research issues be addressed?*

Briefly, we will determine the mean medication costs per patient and compare this between the intervention and control groups. We will use these data to estimate the cost implications of widespread implementation of this model using Ontario prescribing data (for public assistance recipients) from the Institute of Clinical and Evaluative Sciences and Canadian prescribing data from IMS Brogan. We will also assess any implications of health outcome changes (including projected impact on clinical outcomes such as mortality) and changes in healthcare resource limitation. The team includes several health economists (see section 3.2).

#### *2.11 What is the proposed sample size and justification?*

Based on previous studies [29, 48, 49] we expected that between 40% and 60% of patients in the control group will be appropriately adherent. We expect that at least 90% of patients in the intervention group will be compliant (i.e. accept the free medications offered in the intervention). We believe that a 10% absolute improvement in appropriate adherence (in the presence of non-compliance) is the minimal difference that is clinically important. Assuming a Type I error probability of 5%, a sample size of 392 per group is required to have 80% power to detect a 10% absolute difference in adherence for any control group adherence values between 40% and 60%. No inflation for drop-out is applied since drop-outs will be considered non-adherent. Based on previous trials we expect the drop-out rate to be approximately 5 %.[29, 48, 49]

#### *2.12 What is the planned recruitment rate? How will the recruitment be organized?*

We project a recruitment rate of 75 patients per week based on a chart review and on completed RCTs.[29,48,49] Thus recruitment should require less than three months.

Participants will be recruited during routine primary care visits. Based on our chart review, primary care providers see at least 320 unique patients per week (approximately 4 per hour) and approximately 20 % of encounters involve a prescription for a medication. If 20 % of these 64 patients per week who receive a prescription medication are approached by an embedded study research assistant (32 approaches per week), and 20 % are eligible (i.e. report cost-related nonadherence), then 2-4 patients per clinician will be eligible to participate. If 50 % of eligible patients agree to enroll in the study (to have a chance of receiving medications for free), each clinician will recruit approximately 1-2 patients per week.

There are a total of 50 full time equivalent clinicians at the three sites. Thus approximately 75 patients can be recruited each week.

This estimate is conservative as it assumes: that approaches will only take place in encounters involving a prescription medication while care providers may choose to approach patients at other encounters (e.g. a patient on a long term medication who has not presented for a prescription), a moderate approach rate, a low rate of self-reported cost-related non-adherence and a low rate of agreement to participate in a trial of receiving medications for free.

### *2.13 Are there likely to be any problems with compliance?*

The primary outcome is medication adherence by patients. In this trial, “compliance” with the intervention refers to participants deciding to receive the essential medications without charge rather than taking the medications they were previously taking. We anticipate that few patients will choose to enroll in this study but then choose not to take *any* medications provided for free. Some participants may choose to take some medications from the list of essential medications and to also take medications that are not on the list (and this will not pose a problem for the trial). For the sample size calculation, we have assumed a compliance rate of 90 % for the intervention group.

### *2.14 What is the likely rate of loss to follow up?*

We expect a low loss to follow up rate because participants are established patients of family practices. Medication adherence from written prescriptions, prescribing appropriateness and cost analyses can be assessed using information extracted directly from electronic medical records regardless of patient follow-up. The rate of being lost to follow up ranged from 5 to 16 % in the control group and between 5 and 11 % in the intervention group of previous trials.

| Study  | Control   | Intervention | Reasons                                                  |
|---------------|------------------|---------------------|-----------------------------------------------------------------|
| Choudhry 2011 | 151/3010 (5.0 %) | 133/2845 (4.7 %)    | Participants lost insurance coverage                            |
| Farooq 2011   | 9/55 (16.4 %)    | 6/55 (10.9 %)       | Drop out, died, discontinued intervention, withdrew consent     |
| Thom 2013     | 50/1002 (5.0 %)  | 47/1002 (4.7 %)     | Deaths, refused further participation, unable to contact, other |

If a participant leaves the primary care practice, we will attempt to obtain the name of the new care provider and obtain the chart for review. If a participant has left the primary care practice and we are unable to contact them, we will censor the data from that participant after they have left the primary care practice.

### *2.15 How many centers will be involved?*

The trial will be conducted in one urban family practice affiliated with St. Michael’s Hospital in Toronto and two rural family practices in Ontario: Blind River and Manitoulin Island. All sites meet specifications including the use of the same electronic medical record system.

### *2.16 What is the proposed type of analyses?*

Patient demographics will be summarized descriptively (e.g. means and SD or median IQR for continuous variables and frequency and percentages for categorical). Although randomization guarantees balance in the long-run, there is a chance of imbalances in any sample. The demographics will be reviewed for clinically important imbalances that may be adjusted for in a secondary analysis.

The primary analysis will be performed on an intention to treat basis. All patients can be included since drop-outs or withdrawals will be considered non-adherent. Appropriate adherence will be compared using a chi-square test and the unadjusted treatment effect will be expressed as the absolute risk difference with 95% confidence interval. For the primary analysis a p-value of

<0.05 will be sufficient to reject the null hypothesis of no difference. Adjusted analyses will employ logistic regression and the adjusted (conditional) treatment effect will be expressed as an odds ratio with 95% confidence interval.

The first two secondary outcomes are binary at the level of prescription within patient. This will be aggregated to the patient level and logistic regression will be used to compare groups. HbA1C, blood pressure and LDL cholesterol are all continuous and measured at baseline and 9-12 months. An analysis of covariance (ANCOVA) model will be used (via linear regression) to provide the estimates of treatment effect adjusted for baseline values. Since these are all secondary analyses which are supportive or exploratory, no corrections for multiple testing will be applied and only patients with data will be included. However the ITT approach is still followed as patients will remain allocated to their randomized groups irrespective of compliance.

*2.17 What is the proposed frequency of analyses?*

Analysis will occur at the completion of the study when all data are collected. No interim analyses are planned.

*2.18 Are there any planned subgroup analyses?*

We will determine if the effects on medication adherence and health outcomes differ by age and sex.

*2.19 Has any pilot study been carried out using this design?*

The intervention is complex and substantial resources have been dedicated to its development. We have verified the feasibility of chart reviews similar to those that will be used for outcome ascertainment. We believe that a full trial of the intervention is warranted (see *section 1.1*).

### **3. Trial Management**

*3.1 What are the arrangements for the day to day management of the trial?*

The study will be coordinated from St Michael's Hospital in Toronto. The clinical sites will have site research coordinators who will be responsible for recruitment, training of clinicians and patients, and data collection for the duration of the project. They will liaise with a clinical research coordinator in Toronto who will review their data and provide further instructions as required. The lead clinical research coordinator will also be responsible for liaising with the pharmacist, REB board, principal investigators and safety committees. The research team will receive trial implementation assistance from the Applied Health Research Centre (AHRC) who will advise on trial coordination, site training, site start-up/activation, document management, supply management, database development, data management and statistical analysis. The AHRC has experience managing more than 50 multi-site, national and international studies including 15 CIHR-funded multi-centre trials and has grown to be one of the largest academic research organizations in Canada.

Study data and patient questionnaires will be entered and maintained on a secure password protected database developed using Medidata RAVE ([www.mdsol.com](http://www.mdsol.com)) and will be accessible via the internet for data entry purposes. Quality and completeness of data entry will be reviewed as soon as possible after data entry, within 5 business days of data entry for the first 5 participants randomized at each site, and within 15 days of data entry thereafter. Corrections or changes in the data management system will be tracked with the retention of the original data and the corrected data with the date of data entry and submitting personnel.

*3.2 What will be the role of each principal applicant and co-applicant proposed?*

The co-principal investigator [name] (Canada Research Chair in Health Policy and Citizen Engagement and Executive Director, Li Ka Shing Knowledge Institute) is mentoring the principal applicant [name] through a CIHR RCT training grant to develop this trial.

### **Summary of changes to CLEAN Meds trial protocol**

The duration of the trial was extended from 12 months to 24 months when additional funding was secured.

For the analysis of the primary outcome, we originally planned to use electronic pill bottle cap devices in one-seventh of participants to confirm adherence measurements but due to a large amount of missing data in both arms after 12 months, we stopped using the electronic pill bottle cap devices.

We added details about the healthcare cost data collection.

# **CLEAN Meds trial statistical analysis plan**

## **Date: 20 April 2016**

### **Research question**

Does providing convenient access to a carefully selected set of essential medications for free to adult primary care patients increase appropriate medication adherence?

### **Trial design**

Open label, parallel two arm, superiority, individually randomized controlled trial with 1:1 allocation.

### **Outcomes**

*Primary outcome:* Proportion (%) of patients who appropriately adhered to all prescribed treatments (i.e. were adherent to all prescriptions deemed appropriate).

*Secondary outcome:*

1. Proportion (%) of prescriptions that are appropriate.
2. Proportion (%) of prescriptions that are adhered to.
3. HbA1c levels in patients with diabetes (adjusted for baseline).
4. Blood pressure in hypertensive patients (adjusted for baseline).
5. LDL cholesterol levels in patients taking a statin (adjusted for baseline).
6. Per capita medication costs.

### **Treatment and follow up period**

The treatment period will be for 12 months for each patient. (In a separate study, we hope to continue providing patients with these medications for free after the 12 months.)

The follow up period is identical to the treatment period (and so will also be 12 months for all participants). The 12 months of treatment and outcome assessment allows for the evaluation of clinical outcomes and cumulative costs adequately. Medication adherence and health outcomes data (blood pressure, HbA1c levels and cholesterol levels) will be collected during regularly scheduled appointments. Inappropriate prescribing, prescription records and costs will be reviewed from the electronic medical records.

### **Sample size calculation**

Based on previous studies we expected that between 40% and 60% of patients in the control group will be appropriately adherent. We expect that at least 90% of patients in the intervention group will be compliant (i.e. accept the free medications offered in the intervention). We believe that a 10% absolute improvement in appropriate adherence (in the presence of non-compliance)

is the minimal difference that is clinically important. Assuming a Type I error probability of 5%, a sample size of 392 per group is required to have 80% power to detect a 10% absolute difference in adherence for any control group adherence values between 40% and 60%. No inflation for drop-out is applied since drop-outs will be considered non-adherent. Based on previous trials we expect the drop-out rate to be approximately 5 %.

The primary outcome is medication adherence by patients. In this trial, “compliance” with the intervention refers to participants deciding to receive the essential medications without charge rather than taking the medications they were previously taking. We anticipate that few patients will choose to enroll in this study but then choose not to take *any* medications provided for free. Some participants may choose to take some medications from the list of essential medications and to also take medications that are not on the list (and this will not pose a problem for the trial). For the sample size calculation, we have assumed a compliance rate of 90 % for the intervention group.

### **Patient characteristics**

Patient demographics will be summarized descriptively (e.g. means and SD or median IQR for continuous variables and frequency and percentages for categorical). Although randomization guarantees balance in the long-run, there is a chance of imbalances in any sample. The demographics will be reviewed for clinically important imbalances that may be adjusted for in a secondary analysis.

### **Primary outcome**

The primary analysis will be performed on an intention to treat basis. All patients can be included since drop-outs or withdrawals will be considered non-adherent. Appropriate adherence will be compared using a chi-square test and the unadjusted treatment effect will be expressed as the absolute risk difference with 95% confidence interval. For the primary analysis a p-value of <0.05 will be sufficient to reject the null hypothesis of no difference. Adjusted analyses will employ logistic regression and the adjusted (conditional) treatment effect will be expressed as an odds ratio with 95% confidence interval.

### **Secondary outcomes**

The first two secondary outcomes are binary at the level of prescription within patient. This will be aggregated to the patient level and logistic regression will be used to compare groups. HbA1C, blood pressure and LDL cholesterol are all continuous and measured at baseline and 9-12 months. An analysis of covariance (ANCOVA) model will be used (via linear regression) to provide the estimates of treatment effect adjusted for baseline values. Since these are all secondary analyses which are supportive or exploratory, no corrections for multiple testing will be applied and only patients with data will be included. However the ITT approach is still followed as patients will remain allocated to their randomized groups irrespective of compliance.

# **CLEAN Meds trial statistical analysis plan**

## **Date: 9 September 2019**

### **Research question**

Does providing convenient access to a carefully selected set of essential medications for free to adult primary care patients increase appropriate medication adherence?

### **Trial design**

Open label, parallel two arm, superiority, individually randomized controlled trial with 1:1 allocation.

### **Outcomes**

*Primary outcome:* Proportion (%) of patients who appropriately adhered to all prescribed treatments (i.e. were adherent to all prescriptions deemed appropriate).

*Secondary outcome:*

1. Proportion (%) of prescriptions that are appropriate.
2. Proportion (%) of prescriptions that are adhered to.
3. HbA1c levels in patients with diabetes (adjusted for baseline).
4. Blood pressure in hypertensive patients (adjusted for baseline).
5. LDL cholesterol levels in patients taking a statin (adjusted for baseline).
6. Per capita healthcare costs.

### **Treatment and follow up period**

The treatment period will be for 24 months for participants in the control arm and 36 months for participants in the intervention arm.

For the primary analysis, the follow up period is 24 months for all participants. Medication adherence and health outcomes data (blood pressure, HbA1c levels and cholesterol levels) will be collected during regularly scheduled appointments. Inappropriate prescribing, prescription records and costs will be reviewed from the electronic medical records. The total follow up period is identical to the treatment period.

### **Sample size calculation**

Based on previous studies we expected that between 40% and 60% of patients in the control group will be appropriately adherent. We expect that at least 90% of patients in the intervention group will be compliant (i.e. accept the free medications offered in the intervention). We believe that a 10% absolute improvement in appropriate adherence (in the presence of non-compliance) is the minimal difference that is clinically important. Assuming a Type I error probability of 5%,

a sample size of 392 per group is required to have 80% power to detect a 10% absolute difference in adherence for any control group adherence values between 40% and 60%. No inflation for drop-out is applied since drop-outs will be considered non-adherent. Based on previous trials we expect the drop-out rate to be approximately 5 %.

The primary outcome is medication adherence by patients. In this trial, “compliance” with the intervention refers to participants deciding to receive the essential medications without charge rather than taking the medications they were previously taking. We anticipate that few patients will choose to enroll in this study but then choose not to take *any* medications provided for free. Some participants may choose to take some medications from the list of essential medications and to also take medications that are not on the list (and this will not pose a problem for the trial). For the sample size calculation, we have assumed a compliance rate of 90 % for the intervention group.

### **Patient characteristics**

Patient demographics will be summarized descriptively (e.g. means and SD or median IQR for continuous variables and frequency and percentages for categorical). Although randomization guarantees balance in the long-run, there is a chance of imbalances in any sample. The demographics will be reviewed for clinically important imbalances that may be adjusted for in a secondary analysis.

### **Primary outcome**

The primary analysis will be performed on an intention to treat basis. All patients can be included since drop-outs or withdrawals will be considered non-adherent. Appropriate adherence will be compared using a chi-square test and the unadjusted treatment effect will be expressed as the absolute risk difference with 95% confidence interval. For the primary analysis a p-value of  $<0.05$  will be sufficient to reject the null hypothesis of no difference. Adjusted analyses will employ logistic regression and the adjusted (conditional) treatment effect will be expressed as an odds ratio with 95% confidence interval. Participants prescribed no regularly taken medicines (those taking only as needed medicines) were considered nonadherent on the assumption that adherence data for regular medicines may have been missing; a sensitivity analysis was performed to assess the effect of this assumption.

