### *2.3 What are the proposed practical arrangements for allocating participants to trial groups?*

This is a double arm RCT at one urban and two rural sites. A randomization schedule for each site will be generated by computer to ensure allocation concealment. After a participant has provided informed consent, the site research coordinator will allocate the patient to one of the two groups using the allocation sequence from a computer generated random sequence.

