### **Secondary outcomes**

The first two secondary outcomes are binary at the level of prescription within patient. This will be aggregated to the patient level and logistic regression will be used to compare groups. HbA1C, blood pressure and LDL cholesterol are all continuous and measured at baseline and 9-12 months. An analysis of covariance (ANCOVA) model will be used (via linear regression) to provide the estimates of treatment effect adjusted for baseline values. Since these are all secondary analyses which are supportive or exploratory, no corrections for multiple testing will be applied and only patients with data will be included. However the ITT approach is

still followed as patients will remain allocated to their randomized groups irrespective of compliance.

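### Patients are randomised from a separate schedule at each of three sites, but the primary test, the risk difference and the ANCOVA do not account for site: a free improvement

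*Supplement*

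**What the plan says.** **Design.** Section 2.3 of the current (24-month) protocol states: "This is a double arm RCT at one urban and two rural sites". It continues: "A randomization schedule for each site will be generated by computer to ensure allocation concealment". The SAP of 9 September 2019 (Trial design) gives 1:1 individual allocation. Neither document says whether the schedules are blocked within site.

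**Primary analysis.** The SAP (Primary outcome) states: "Appropriate adherence will be compared using a chi-square test and the unadjusted treatment effect will be expressed as the absolute risk difference", with a 95% confidence interval. Protocol section 2.16 agrees.

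**Secondary analyses.** The SAP (Secondary outcomes) fits ANCOVA models to HbA1c, blood pressure and LDL "to provide the estimates of treatment effect adjusted for baseline values"; no other covariate is named. The two prescription outcomes are aggregated to the patient level and compared by logistic regression, again with no covariate named.

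**Adjusted analyses.** The SAP adds: "Adjusted analyses will employ logistic regression and the adjusted (conditional) treatment effect will be expressed as an odds ratio with 95% confidence interval". Their covariates are not listed. Under Patient characteristics it says: "The demographics will be reviewed for clinically important imbalances that may be adjusted for in a secondary analysis".

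Site is not named in any planned analysis.

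**The concern.** A factor used to stratify randomisation is normally carried into the analysis. When arms are balanced within strata, the estimated difference no longer varies through chance differences in site mix. An unstratified standard error still counts that variation, so it is too large whenever site predicts the outcome.

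Site could plausibly predict the outcome here. Chart-review adherence depends on whether a renewal is written within 18 days of the expected date (section 2.9), so a practice's renewal habits enter the endpoint directly. Delivery can also differ: rural sites may use local partner pharmacies and local staff for home visits (section 2.2).

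What is at stake is efficiency. The test could be a little too cautious and the interval a little too wide, in a trial sized with almost no spare power.

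**Working it through.** **1. Reproduce the plan's sample size.** Inputs from the SAP (Sample size calculation): type I error 5%, power 80%, a 10-point difference, control rate 40% to 60%. A two-sided test is assumed, since sidedness is not stated. The worst case is 45% v 55%. With pooled variance under the null:

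n = [1.960 × √(2 × 0.5 × 0.5) + 0.842 × √(0.45 × 0.55 + 0.55 × 0.45)]² / 0.10² = 391.3, so 392 per group.

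This matches the plan. Power at 392 is 0.801, the minimum over control rates of 40% to 60%.

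**2. Size of the standard-error excess if arms are balanced within site.** The crude variance is based on p(1 − p) overall. The correct variance removes the between-site part, so

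correct SE / crude SE = √(1 − B/T), with T = p(1 − p) and B = w(1 − w)g²,

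where w is the urban share and g the gap between the urban site and both rural sites. The true type I error of the crude test is 2 × [1 − Φ(1.960 ÷ ratio)].

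The documents give neither w nor g, so these are **assumptions**: shares of 70/15/15% or 50/25/25%, and gaps of 0 to 40 points. The control rates (urban/rural) are 45/45, 42/52, 39/59, 36/66 and 30/70%.

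Example, 70/15/15% and a 30-point gap: p = 0.7 × 0.36 + 0.3 × 0.66 = 0.45, T = 0.2475, B = 0.7 × 0.3 × 0.09 = 0.0189. The ratio is √(1 − 0.0764) = 0.961, and the type I error is about 4.1%.

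**3. Simulation.** 40,000 trials per scenario, 784 patients, arms equal within site. The crude chi-square is compared with the site-stratified Cochran-Mantel-Haenszel (CMH) test; power and coverage are at a 10-point effect. Each cell gives 70/15/15% first, then 50/25/25%.

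| Gap (points) | Crude type I, formula (%) | Crude type I, simulated (%) | CMH type I (%) | Crude power (%) | CMH power (%) | Crude CI coverage (%) |
|---|---|---|---|---|---|---|
| 0 | 5.0; 5.0 | 4.7; 4.8 | 4.7; 4.8 | 80.0; 79.7 | 80.0; 79.7 | 95.1; 95.0 |
| 10 | 4.9; 4.9 | 4.8; 4.8 | 4.9; 4.8 | 79.9; 80.3 | 79.9; 80.3 | 95.2; 95.2 |
| 20 | 4.6; 4.6 | 4.5; 4.4 | 5.1; 4.9 | 80.6; 80.7 | 81.8; 82.2 | 95.5; 95.6 |
| 30 | 4.1; 4.0 | 4.1; 4.0 | 5.1; 5.0 | 80.5; 81.4 | 82.7; 84.2 | 96.0; 96.0 |
| 40 | 3.5; 3.3 | 3.5; 3.1 | 5.1; 5.0 | 81.8; 82.1 | 85.8; 86.9 | 96.7; 97.1 |

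Simulation error (one standard error) is about 0.1 point for type I error, √(0.05 × 0.95 / 40,000), and 0.2 point for power, √(0.8 × 0.2 / 40,000). Formula and simulation agree.

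**4. The same scenarios with simple randomisation within site.** The crude type I error stays at 4.9% to 5.2% and that of CMH at 4.9% to 5.2%. Crude power is 79.9% to 80.7%. Stratifying gains at most 0.4 point at gaps up to 10 points, 1.2 to 1.4 points at 20, 3.0 to 3.4 at 30 and 5.4 to 6.0 at 40.

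**5. ANCOVA.** The documents give no standard deviations or site means, so the gain from a site term cannot be sized. The baseline value will already absorb part of any site difference.

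**The case against.** The strongest reply is that the planned analysis is valid and transparent, and that stratifying is an efficiency choice. Much of this stands.

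- **The conservatism depends on a fact not stated.** It arises only if arms are balanced within site. The protocol gives allocation concealment as the reason for per-site schedules and does not mention blocks. Without balance, the crude test holds its level. The recommendation survives, because stratifying gains power in that case too.
- **The magnitude rests on assumed gaps.** At 10 points or less there is almost nothing to gain, and gaps of 30 to 40 points would be large.
- **Planned power is met.** The crude test has about 80% power or more throughout, within simulation error. The gain is a bonus over the plan.

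Three stronger readings might be inferred, and the documents do not support them.

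- **That imbalance-driven adjustment compromises the primary result.** The SAP confines it to a secondary analysis and fixes the primary test and effect measure. What remains is that the adjusted logistic model lists no covariates, a gap in a supportive analysis.
- **That reporting "the adjusted (conditional) treatment effect will be expressed as an odds ratio with 95% confidence interval" beside a risk difference is an error.** The SAP labels the estimate conditional, keeps the risk difference as primary and never proposes to compare the two scales. Another scale would be a preference.
- **That the SAP excludes site from every model.** In the adjusted logistic analysis the covariates are unnamed, so site is unspecified there, not ruled out.

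**Conclusion.** The mismatch is real: allocation is by site, while the primary test, the risk difference and the ANCOVA do not use site. The consequence is limited to efficiency. It would be wrong to infer a biased estimate, an inflated false-positive rate or an underpowered trial; the calculations show none of these.

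With balanced arms within site and the assumed shares, stratifying adds about nil power at gaps of 0 to 10 points, 1 to 1.5 points at 20, 2 to 3 at 30 and 4 to 5 at 40. Over the same range the crude type I error falls to about 3.1% to 3.5%, and interval coverage rises to about 97%. With simple randomisation within site the level stays at about 5%, and the gain in power is similar or slightly larger. The sample size of 392 per group needs no change. This is a free improvement and does not threaten the trial's conclusion.

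**What to change.** In the SAP (Primary outcome) and protocol section 2.16, replace the crude comparison with a Cochran-Mantel-Haenszel test stratified by site, and report the site-stratified absolute risk difference with its 95% CI. In the SAP (Secondary outcomes), add site as a covariate to the ANCOVA models and to the patient-level logistic models for the first two secondary outcomes.

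The cost is one or two sentences: site is known for every patient, and no extra data or patients are needed. The change should be fixed before results by arm are seen. If they have been seen already, the stratified analysis belongs alongside the planned one as a sensitivity analysis. Stating in section 2.3 whether the schedules are blocked would settle which case applies, but the fix does not depend on it.
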